### Sample size/power calculation

#### Sample size considerations

Sample size considerations in clinical studies start from what is considered a MCID. In studies of chronic LBP, the ODI is commonly used as the main outcome measure, and a difference in 10 ODI points is considered clinically relevant. We will consider the sample size and power according to the MCID of ODI.

A minimum of 10 patients with chronic LBP are needed to produce stable estimates for each predicting variable. We will collect data on e.g. 20 potential predictive factors and screen these by logistic regression. If assuming we select four of these predictors for regression modelling, looking for an independent effect, then at least 40 patients with chronic LBP will be needed, 10 patients for each predictor.

We considered a series of scenarios for sample size calculations which resulted in an array of sample sizes between 200 and 800 patients necessary to ensure 80% power at a two-sided p of 0.05. If 5% of patients with acute LBP develop chronic LBP, 800 patients will have to be analysed. However, if 10% or 20% develop chronic LBP at 6 months follow-up only 400 and 200 patients respectively will be needed. Trends from our pilot study including 20 patients in Otago district, NZ show that an even smaller sample size might be sufficient – due to a rate of chronic patients of up to 30% in the pilot sample.

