### Outcome assessment

#### Demographic and baseline characteristics

The following demographic, biomedical, psychological, social, and occupational factors will be assessed at baseline according to the recommendations of the MMICS Statement:

- Gender [34,35]

- Age [32,36-38]

- BMI

- Ethnicity

- ODI [39,40]

- Acute SF-12 [41]

- Quality and intensity of LBP (SF-McGill including VAS) [42-44]

- LBP history (duration and recurrence) [45-48]

- Radiating leg pain below the knee

- Lifestyle factors (exercise, smoking, alcohol consumption) [49-52]

- Depression (modified self-rating depression scale by Zung ZUNG) [53,54]

- Somatisation (Modified Somatic Perceptions Questionnaire MSPQ) [55]

- Fear avoidance beliefs (Fear Avoidance Beliefs Questionnaire FABQ) [56-58]

- Pain catastrophizing (Pain Catastrophizing Scale PCS) [59]

- Marital/relationship status

- Social support

- Educational status

- Employment/work status

- Job satisfaction [35,60-62]

- Job control [35,63]

- Work stress factors [61,62,64-67]

- Belief that work has caused LBP [68-70]

- Duration of work-absenteeism [9,71-73]

- Reasons for not working

- Disability compensation status [74-79]

- Patients' expectations on return to work [80-82].

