### Statistical analysis

#### Multivariate identification of predictors for chronicity

Changes in primary and secondary endpoints between baseline data and different time points of follow-up will be analysed by multiple linear regression models. Patients with chronic LBP at 6 months follow-up will be compared with patients without chronic LBP at the same time point.

Patients with chronic LBP in this study are defined as patients with an ODI score without improvement by a Minimal Clinically Important Difference (MCID) of 10 ODI points between T0 (attending the GP for the first time or after a pain free period of at least 6 months) and T4 (6 months follow-up) [84-87].

An analysis of different assessment instruments and baseline characteristics will be performed to find appropriate scores or patient characteristics to identify patients at risk to develop chronic LBP. Different patient assessment tools will be allocated to the following four groups: demographic-biomedical, psychological, social, and occupational risk group [88]. We aim to detect at least one assessment instrument in each group which identifies patients at risk.

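### The sample size counts events only for the four predictors kept after screening about 20, so its 40-event minimum gives 2 events per candidate and the selected model is likely to look better than it is

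*Protocol article*

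**What the plan says.** All of the sizing is in the protocol article, under Sample size considerations. The rule is "A minimum of 10 patients with chronic LBP are needed to produce stable estimates for each predicting variable". The modelling steps are "We will collect data on e.g. 20 potential predictive factors and screen these by logistic regression", followed by "If assuming we select four of these predictors for regression modelling". The rule is then applied to the four: "at least 40 patients with chronic LBP will be needed, 10 patients for each predictor".

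The patient numbers follow: "If 5% of patients with acute LBP develop chronic LBP, 800 patients will have to be analysed", and "if 10% or 20% develop chronic LBP at 6 months follow-up only 400 and 200 patients respectively will be needed". The section adds that fewer patients still may be enough, because up to 30% were chronic in a pilot of 20.

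Three other sections bear on this:
- Demographic and baseline characteristics introduces its list with "The following demographic, biomedical, psychological, social, and occupational factors will be assessed at baseline". The list has 26 entries, and some hold several variables (for example exercise, smoking and alcohol under lifestyle).
- Multivariate identification of predictors for chronicity sets an aim for the four groups of instruments: "We aim to detect at least one assessment instrument in each group which identifies patients at risk".
- Data collection expects 792 patients to be analysed, after allowing for 20% loss to follow-up.

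**The concern.** An events-per-variable rule is a guide to stability when the variables in the model are fixed in advance. Here they are not. About 20 factors are compared with the outcome, and the ones that look strongest are carried into a model fitted to the same patients. Factors whose observed association happens to be too large are more likely to be kept. The refitted odds ratios then tend to be too large, their intervals too narrow and the discrimination too high. Counting only the survivors hides this, and the promise of stable estimates does not carry over to a model chosen in this way.

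The intended product is a screening tool for general practice. If its reported performance is optimistic, it will do worse in new patients than the publication says. The remark that fewer patients may suffice adds to the risk, since it would allow recruitment to stop early on the strength of a count that leaves out the selection step.

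**Working it through.** **Inputs.** From Sample size considerations: 10 events per variable, 20 candidates (given as an example), 4 kept (an assumption), and chronicity of 5%, 10%, 20% and up to 30% (pilot). From Data collection: 792 analysed. From the baseline list: 26 entries.

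**The plan's own figures.** Events = 10 × 4 = 40, and patients = events / chronicity:
- 40/0.05 = 800
- 40/0.10 = 400
- 40/0.20 = 200

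All three reproduce exactly. At the pilot's 30%, 40/0.30 is about 133, which is what the remark about a smaller sample would imply.

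**Events per candidate at the minimum.** 40/20 = 2.0 at every one of these sizes, including 133. With the 26 listed entries it is 40/26 = 1.5.

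**Events per candidate with 792 analysed.**

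| Chronicity | Events (792 × rate) | Per candidate (÷ 20) | If 792 is per country (1,584 × rate ÷ 20) |
|---|---|---|---|
| 5% | 39.6 | 2.0 | 4.0 |
| 10% | 79.2 | 4.0 | 7.9 |
| 20% | 158.4 | 7.9 | 15.8 |
| 30% | 237.6 | 11.9 | 23.8 |

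**The same rule counted over candidates.** 10 × 20 = 200 events, which is 4,000, 2,000, 1,000 and 667 patients at 5%, 10%, 20% and 30%.

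**What selection does.** A simulation used 20 normally distributed candidates with mutual correlation 0.2. The four with the largest univariable test statistics were kept and refitted, with 120 runs per setting. The effect sizes and the univariable form of the screen are assumptions; the article gives neither. A calibration slope of 1 means no overfitting, and lower values mean more.

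| True effects | Sample | Apparent AUC | True AUC | Slope, four selected from 20 | Slope, four prespecified |
|---|---|---|---|---|---|
| None | 40 events (800/400/200) | 0.65–0.66 | 0.50 | about 0 | about 0 |
| Four, log OR 0.3 per SD | 40 events | 0.73 | 0.65–0.66 | 0.62–0.67 | 0.79–0.85 |
| Four, log OR 0.5 per SD | 40 events | 0.81 | 0.76–0.79 | 0.79–0.89 | 0.88–0.96 |
| Four, log OR 0.3 per SD | 792, 10–30% | 0.70–0.71 | 0.68 | 0.81–0.91 | 0.87–0.94 |
| Four, log OR 0.5 per SD | 792, 10–30% | 0.79–0.80 | 0.78–0.79 | 0.93–0.98 | 0.93–1.00 |

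The second row isolates the problem. Both models have 10 events per final predictor, yet the slope falls from 0.79–0.85 to 0.62–0.67 when the four are selected from 20 rather than fixed beforehand.

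**The case against.** The best defence is that the plan makes no arithmetical error and applies its rule consistently. The rule refers to predicting variables, and the plan counts those in the final model. This stands: a reader might infer that the plan breaks its own rule, but the wording does not say that. Counting candidates is sound practice that goes beyond what the plan states.

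Two events per candidate describes the stated minimum, not necessarily the study. With 792 analysed, that ratio applies only at 5% chronicity. At the pilot's upper rate of 30%, even ten per candidate is met for 20 candidates. Data collection can also be read as giving 792 per country, which would double every ratio. This stands too, although a pilot of 20 patients is weak support for 30%. The 10% quoted in Background rests on a different definition of chronicity from the disability-score definition used here.

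The figures 20 and four are illustrative. The article gives no entry threshold, so the often-used calculation 1 − 0.95^20 = 0.64 for at least one false positive depends on independent tests at 0.05, which it does not state. A simulation with noise only is an extreme case, since many of the listed factors come with supporting literature.

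A reader might also count the lack of shrinkage or validation as a fault. This is a condensed article and an analysis plan may cover both, so that is not part of the point. Likewise, finding one instrument per group is stated as an aim, and nothing forces an instrument to be kept.

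Finally, the Statistical analysis section names multiple linear regression for changes in the endpoints. Events per variable does not govern that model, so the point concerns only the logistic screening and modelling on which the sample size is based.

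**Conclusion.** The point holds in a limited form. The 40-event minimum behind 800, 400 and 200 patients, and behind the suggestion that fewer may do, leaves out the selection step and gives 2 events per candidate for 20 candidates. It does not support stable estimates after selection on the data, and optimism is likely, especially at low chronicity.

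How much optimism cannot be fixed from the document. With 792 analysed, the ratio runs from about 2.0 to 11.9 per candidate between 5% and 30% chronicity. Under the assumed effects, the slope runs from 0.62 at 40 events with weak predictors to 0.98 at 792 patients with stronger ones. The stronger conclusion, that the model is bound to be badly overfitted, is therefore not supported: it is plausible near 5% chronicity with weak predictors and unlikely at 30% with strong ones. The ratios assume 20 candidates with one parameter each; multi-category or multi-item factors would lower them.

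**What to change.** State the events rule per candidate parameter. Withdraw the statements that 40 events, or a still smaller sample, are enough when 20 factors are screened. Then take one of two routes, neither of which needs more patients:

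- **Shorter list.** Prespecify no more candidate parameters than expected events/10. With 792 analysed that is 39.6/10, 79.2/10 or 158.4/10, or about 4, 8 or 16 parameters at 5%, 10% or 20% chronicity.
- **Penalised model.** Replace screening and refitting with one penalised logistic model (LASSO or ridge) containing all candidates. Bootstrap the whole selection process, and report the optimism-corrected AUC and calibration slope.

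State also whether 792 is the total or per country, because the permitted list length depends on it. Recruiting to 200 events is not required, and the one-instrument-per-group aim can stay as an aim.

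The cost is some programming and revised wording. The reported performance will be less favourable, and under the first route some factors will be left out of the model.

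### The 200, 400 and 800 patients said to ensure 80% power are 40 events divided by the chronicity rate; the 80% power is not derived, and no target effect is stated

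*Protocol article*

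**What the plan says.** All of this is in the protocol article under Sample size considerations. The section opens by naming a 10-point ODI difference as clinically relevant and announces: "We will consider the sample size and power according to the MCID of ODI". It then changes to a different rule: "A minimum of 10 patients with chronic LBP are needed to produce stable estimates for each predicting variable". With four predictors kept for the model, "then at least 40 patients with chronic LBP will be needed, 10 patients for each predictor". These four are to come from a larger pool: "We will collect data on e.g. 20 potential predictive factors and screen these by logistic regression".

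The results follow. Scenarios are said to have given "an array of sample sizes between 200 and 800 patients necessary to ensure 80% power at a two-sided p of 0.05", and the individual sizes are: "If 5% of patients with acute LBP develop chronic LBP, 800 patients will have to be analysed"; "if 10% or 20% develop chronic LBP at 6 months follow-up only 400 and 200 patients respectively will be needed". The section ends by suggesting that fewer patients might be enough, because up to 30% of 20 pilot patients were chronic. It gives no odds ratio, standard deviation, predictor prevalence or correlation between predictors.

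The Data collection section separately expects 792 patients to be analysed.

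**The concern.** A power figure means something only for a stated effect. Here the figure is attached to sizes that appear to come from a rule about stable estimation, which has no power in it. The section also names the 10-point ODI difference as its basis, yet that difference does not visibly enter the calculation.

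Two things are at stake. A reader who believes the 80% may take a non-significant predictor as a well-powered negative result. And the closing remark on the pilot lends support to a smaller sample on the strength of a power property that was never shown.

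**Working it through.** **1. Reproducing the stated sizes.** Inputs from Sample size considerations: 10 events per predictor, 4 predictors, chronicity p of 5%, 10% or 20%.

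N = (4 × 10)/p: 40/0.05 = 800; 40/0.10 = 400; 40/0.20 = 200. All three are exact. Neither the 0.05 level nor the 80% is used.

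**2. Could one power calculation give the same three sizes?** For a fixed effect, the information in a chronic versus non-chronic comparison is proportional to N·p·(1−p). Equal power therefore needs N proportional to 1/[p(1−p)]. Starting from 200 at 20%, that gives 200 × 0.16/0.09 = 356 at 10% and 200 × 0.16/0.0475 = 674 at 5%, not 400 and 800. No single effect reproduces the set.

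**3. The 10-point ODI difference.** No SD is given, so SD is an assumption. Total N = (1.960 + 0.842)² × (SD/10)² / [p(1−p)].
- SD 20: 196/349/661 for chronicity 20/10/5%.
- SD 15: 110/196/372.

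At SD 20 the totals fall near the stated range but do not match it.

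**4. Power at 40 events.** The effects below are assumptions; the article states none. All are two-sided 0.05 without multiplicity correction.
- Mean difference of 0.5 SD: Φ(0.5/√(1/40 + 1/(N−40)) − 1.96).
- Continuous predictor: Φ(√(N·p(1−p)(1−R²)) × ln OR − 1.96), where N·p(1−p) = 32, 36 and 38, and R² is that with the other predictors.
- Binary predictor, even split, OR 2.0: two-proportion comparison with the overall rate held at p, which gives risks of 14.6% v 25.4%, 7.0% v 13.0% and 3.4% v 6.6%.

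| Assumed effect | N=200, 20% | N=400, 10% | N=800, 5% |
|---|---|---|---|
| 0.5 SD difference, unadjusted | 81% | 85% | 87% |
| OR 1.5 per SD, unadjusted | 63% | 68% | 71% |
| OR 1.5 per SD, R² = 0.3 | 48% | 53% | 55% |
| Binary 50/50, OR 2.0, unadjusted | 49% | 53% | 54% |

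**5. Smallest odds ratio with 80% power at 40 events.**
- Per SD: exp(2.802/√(N·p(1−p)(1−R²))) = 1.64/1.60/1.58 unadjusted and 1.81/1.75/1.72 at R² = 0.3.
- Evenly split binary factor, unadjusted: about 2.8/2.7/2.6.

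**6. At the planned 792 analysed, unadjusted.**

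| Chronicity | Events | OR 1.5 per SD | Binary 50/50, OR 2.0 |
|---|---|---|---|
| 5% | 39.6 | 70% | 54% |
| 10% | 79.2 | 93% | 81% |
| 20% | 158.4 | over 99% | 97% |

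At 10% and R² = 0.3, power for OR 1.5 per SD is 82%.

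**7. The pilot remark.** If up to 30% of 20 means 6/20, the exact 95% interval is 12% to 54% (0.119 to 0.543). Forty events could then need between 40/0.543 = 74 and 40/0.119 = 336 patients. At the implied 40/0.30 = 133, power is 57% for OR 1.5 per SD and 75% for a 0.5 SD difference, both unadjusted.

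**The case against.** The best defence is that the sizes can be reconciled with the ODI difference. The comparison is between a small chronic group and a large remainder, so a calculation with two equal groups would be the wrong yardstick. With the plan's own split and an SD of 20, the stated sizes give 81 to 87% power for 10 points, and more for a smaller SD. The 10-point difference also has a role elsewhere: under Multivariate identification of predictors for chronicity it defines who counts as chronic. This stands, and it rules out any claim that the ODI difference is incompatible with 200 to 800 patients. It does not show that the sizes were derived that way, because no SD is given and step 2 shows that no single effect yields all three.

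A reader might infer that the study is underpowered for moderate predictors. The document does not support that. It defines no moderate effect, and the answer changes with the one chosen: a 0.5 SD difference reaches 80% at 40 events, while an odds ratio of 1.5 per SD does not. The inference also overlooks the 792 patients planned for analysis, which at 10% chronicity, the rate the Background section cites, give about 79 events.

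It can also be said that a journal article condenses its scenarios, that the events rule is openly stated, and that no stopping rule hangs on the pilot remark. All true, and they keep this a matter of wording. But the article prints its inputs and results and attaches to them a property that they do not carry. That is a misstatement, not an omission.

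**Conclusion.** The point holds in a limited form. That the three sizes equal 40 events divided by the chronicity rate is exact and needs no assumption. The 80% power at two-sided 0.05 is not derived from anything stated, and the announced ODI basis is not carried through to the sizes.

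Whether 80% is reached cannot be settled from the document. Under the assumed effects, power at 40 events runs from about 48% (odds ratio 1.5 per SD, R² = 0.3) to 87% (0.5 SD difference, unadjusted, N = 800). At 792 analysed, the shortfall for an odds ratio of 1.5 per SD or an even binary odds ratio of 2.0 persists if chronicity is 5% and largely disappears at 10% or more. These figures take 792 as the total for both countries and make no allowance for screening some 20 candidate predictors; a multiplicity correction would lower them.

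**What to change.** Revise Sample size considerations as follows.

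- State that 200, 400 and 800 rest on 10 events per variable for four predictors.
- Delete the 80% power claim, or replace it with a detectable effect and its assumptions. For example: *Forty events give 80% power (two-sided 0.05, no multiplicity correction) for an odds ratio of about 1.6 per SD unadjusted, about 1.7 to 1.8 if R-squared with the other predictors is 0.3, or about 2.6 to 2.8 unadjusted for an evenly split binary factor; the ranges cover chronicity from 5% to 20%.*
- Stop presenting the 10-point ODI difference as the basis of the sample size. Its use in defining chronicity is unaffected.
- Remove the remark that an even smaller sample might suffice.

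The cost is the rewording of one section and a less favourable statement than the present one. Enrolment does not change.

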### Feasibility of the study

#### Patient recruitment

Patients in NZ will be recruited consecutively and prospectively in collaboration between the Department of Orthopaedic Surgery at Dunedin Hospital, UoO, and Best Practice Advocacy Centre Incorporated (BPAC Inc), Dunedin. GPs cooperating with BPAC Inc will ask patients who meet the study eligibility criteria to give their consent to be contacted by the research group at the UoO to participate in our study. Patients who give their consent may be given a detailed information sheet by their GPs about the study including contact details of the study coordinator. On the same day, contact details (telephone number, postal and email address) of these patients will be electronically forwarded in an automated fashion from the GP clinics to the research group at the UoO.

Patient assessment at different time points in our study will be conducted by research nurses at the UoO. At baseline a short screening interview on the telephone will be performed following a structured questionnaire. This interview will check the eligibility for enrolment (see inclusion criteria, Table 1). When a patient is classified as eligible, a document stating their signed consent and a first set of questionnaires (T0) will be sent out by post on the same day. At follow-up times (T1-4) research nurses will collect these patient-derived questionnaires and enter them into the central database. If not returning the questionnaire a first reminder will be sent out after one and a second after two weeks.

To optimise the number of completed questionnaires patients will be able to choose between a $NZ10 fuel, supermarket or book voucher as compensation for their expenditure of time after return of each of the five questionnaires. This level of compensation will not encourage unwilling participation. GPs will be compensated with the same choice of voucher for every referred patient.

Patients in CH will be recruited consecutively and prospectively at the realHealth Centre, Nottwil. Patient assessment and follow-ups will be conducted in parallel to the study arm in NZ by a research group headed by NA.

### Data collection

2220 patients will be assessed for eligibility in NZ and CH respectively (Figure 1). It can be assumed that 75% of these screened patients will be found eligible for enrolment. Out of these 1650 patients it is estimated that 990 (60%) will agree to participate in this study. Up to 20% of the patients can be expected to be lost to follow-up, in the worst case scenario, so that an estimated 792 patients will be analysed.

**Figure 1 F1:**
[figure not shown]
Recruitment and data collection.

The expected duration of the data collection phase of the study will be two years, comprising one and a half years of patient recruitment overlapping with two years of follow-up.

## Discussion

### Scientific significance

LBP is by far the most prevalent and most costly musculoskeletal problem in our society today [6,10,89,90]. Despite numerous previous studies, to our knowledge there has not been an attempt to comprehensively assess all potential factors which lead to the transition from acute to chronic LBP and the point in the disease progression when this occurs [7].

This study will assess a core set of outcome assessment tools for patients with acute LBP in a GP setting to assess which factors predict whether these patients are at risk of developing chronic LBP [91,92]. In addition, biomedical, psychological, social, and occupational baseline characteristics will be identified which may be found to influence the course from acute to chronic LBP. Furthermore, an appropriate time for follow-ups will be given to increase the likelihood of detecting this transition.

The international perspective of this study of patients in NZ and CH will be an asset in terms of generalizability and validation of our findings for use by others.

